#### Eligibility

##### Inclusion criteria

In order that the results of this randomised clinical trial can be generalised as widely as possible, we propose to include all patients, including those with cognitive impairment, admitted with an intracapsular (displaced or undisplaced) fracture of the proximal femur. This pragmatic approach will mean that any conclusions derived will be widely applicable to clinical practice.

##### Exclusion criteria

• All patients who present late following their injury i.e. more than 48 hours after the index fracture.

• Patients with other serious injuries to either lower limb that would interfere with rehabilitation of the index fracture.

• Patients who are managed non-operatively

#### Post-randomisation withdrawals and exclusions

Participants may withdraw from the trial treatment and/or the whole trial at any time without prejudice. If a participant withdraws from the trial treatment he will be followed-up wherever possible and data collected until the end of the trial.

The General Practitioners of those participants who are "lost-to-follow-up" will be contacted in order to attempt to complete the follow-up. Failing this then the Hip Fracture Register will be consulted in order to try to establish up-to-date participant contact details. Participants may be withdrawn from the trial at the discretion of the Chief Investigator due to safety concerns.

#### Consent

An informed consent discussion will be conducted with potential participants after eligibility checks have been performed but prior to randomisation.

Potential participants will be informed about the nature of the trial by the investigator or persons designated by the investigator. This will involve a discussion of purpose and requirements of the trial and the issuing of the participant information sheet.

Patients will be allowed, where possible, at least twenty four hours to consider the information given them prior to being asked to give informed consent to participate in the trial. This period of time will not be allowed to delay any normal standard of care treatment.

Responsibility for recording and dating both verbal and written, signed informed consent will be with the investigator, or persons designated by the investigator, who conducted the informed consent discussion. The following information will be discussed during the consent discussion:

• Benefits of internal fixation of intracapsular proximal femoral fractures

• Risks of internal fixation of intracapsular proximal femoral fractures

• Impact of allocation to different treatment arms of the trial

• Requirements of follow-up

• Benefits of taking part in the trial

For those patients who lack the capacity to give informed consent reasonable efforts will be made to identify a Personal Consultee as described in the *Mental Capacity Act 2005*. If no personal consultee can be identified then a Nominated Consultee will be nominated to advise the research team. The following persons will be approached in the order given in the list below:

i. The patient's General Practitioner

ii. [name] FRCS(Tr&Orth), Consultant Orthopaedic Surgeon UHCW.

At all times the Chief Investigator will act in accordance with the patients' best interests.

#### Recruitment

Participant recruitment will begin in August 2009 and be completed by August 2010. Pre-randomisation eligibility checks will be carried out to ensure that participants are not randomised in error, and informed written consent will be obtained prior to randomisation. Confirmation of these checks will be carried out by the investigator, or persons designated by the investigator, prior to randomisation. Inclusion of the patient in the trial will be flagged on their clinical notes by means of a trial sticker.

#### Treatment allocation

##### Sequence generation

The allocation sequence will be generated randomly. The randomisation will be weighted such that at the end of the trial there will be 25 participants in the fixed-angle screw and plate group and 100 participants in each of the remaining groups. Randomisation will be stratified by displacement of the fracture. Fractures will be defined as undisplaced (Garden grade I or II) or displaced (Garden grade III or IV); Garden's classification of intracapsular fractures is well recognised and universal and it has been validated to distinguish between grades I and II compared with III and IV [12,13]. The surgery will be performed by any of the 16 Consultant Surgeons, two Associate Specialists and 14 Trainees at the University Hospital Coventry and Warwickshire. The large number of surgeons and the wide skill mix should eliminate the 'surgeon effect' such that stratification by surgeon is not required.

##### Allocation concealment

The allocation sequence will be generated using secure, online randomisation via a distant computer generated system administered by The University of York.

##### Allocation implementation

Participants will be enrolled by the trial research associates, co-ordinated by [name]. Participants will be assigned to their treatment allocation at the time of surgery by accessing the online randomisation programme. This will allow for treatment allocation to be implemented outside of working hours.

#### Blinding

Participants will be blinded to the treatment allocation. The operating surgeon will not be blinded to the allocation. All outcomes will be assessed by blinded assessors. The primary outcome measure will be determined by the clinical decision of the responsible consultant orthopaedic surgeon who is independent from the trial. The responsible consultant surgeon will not be the operating surgeon in order to maintain the blind. The EQ-5D is a patient reported measure. Patients will be kept blinded until the completion of the trial when the blind is broken. Radiographic outcomes will be assessed by an independent consultant radiologist who is blinded to the treatment allocation. There will be no formal analysis of the success of the blinding.

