## Methods

### Trial Design

#### Design summary

This trial will be a three arm single centre, standard-of-care controlled, double blinded, pragmatic, randomised clinical trial.

The study will include a standard two-way comparison between PRP and standard-of-care fixation versus standard-of-care fixation alone. This comparison will be the only hypothesis-testing analysis. In addition there will be a subsidiary pilot arm testing fixed-angle screw and plate fixation. This comparison will be a hypothesis-generating analysis only.

The trial is expected to last a total of two years. It is expected that participant recruitment will take one year and final follow-up will be at one year.

The trial was given ethical approval by the Coventry Research Ethics Committee on 6 May 2009.

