#### Measures of efficacy

##### Primary

• The proportion of participants undergoing re-operation for failure of fixation within one year of sustaining the fracture.

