#### Group 1: Fixed-angle screw and plate fixation

Fixation will be with the Targon FN Head Preserving System as described in the manufacturer's operative technique manual.

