#### Group 2: Standard of care fixation

Fixation will be with three parallel cannulated screws. The exact configuration will be left to the discretion of the operating surgeon to ensure the results can be easily generalised. Fixation will be achieved using the standard operative technique.

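### The blinding claims cover all three arms, but the fixed-angle plate can be told from screws on the radiographs, so the pilot comparison is not assessor-blind

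*Protocol article*

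**What the plan says.** The Design summary gives one blinding label to the entire trial: "This trial will be a three arm single centre, standard-of-care controlled, double blinded, pragmatic, randomised clinical trial". The Design paragraph of the Abstract does the same.

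The Blinding section makes three statements about assessors, none of which excepts an arm:

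- In general: "All outcomes will be assessed by blinded assessors".
- For imaging: "Radiographic outcomes will be assessed by an independent consultant radiologist who is blinded to the treatment allocation".
- For the primary outcome: "The primary outcome measure will be determined by the clinical decision of the responsible consultant orthopaedic surgeon who is independent from the trial". The safeguard given is: "The responsible consultant surgeon will not be the operating surgeon in order to maintain the blind".

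The implants are described separately. For Group 1: "Fixation will be with the Targon FN Head Preserving System". For Group 2: "Fixation will be with three parallel cannulated screws". Group 3 has the same screws as Group 2, plus the PRP injection.

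The section on the fixed-angle comparison rules out formal inference. It still plans to describe the primary event rate and the secondary measures, and to estimate the plate's effect for use in designing later studies.

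**The concern.** A radiologist who has to judge whether a fixation has failed must look at the fixation. If one arm has a plate system and the other has only screws, the image itself reveals the arm. The blinding statements would then be wrong for one of the three groups, and for every comparison that involves it.

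What is at stake is how the pilot result can be described. Exploring the plate's effect is the second of the trial's two stated objectives, and the estimate is meant to feed further designs. Judgements about union, fixation and the need to re-operate leave room for an assessor's expectations about a new device. Under the present wording, the estimate would be carried forward with a safeguard it does not have.

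**Working it through.** No figure in the plan bears on this point. The check sets the sections side by side.

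**1. What differs between the arms**

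| Group | Planned number (Sequence generation) | Implant (Trial treatments) | Injection |
|---|---|---|---|
| 1 | 25 | Fixed-angle screw and plate system | None described |
| 2 | 100 | Three parallel screws | Placebo |
| 3 | 100 | Three parallel screws | PRP |

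**2. What the assessors must look at.** Table 2 schedules AP and lateral radiographs at 6, 12 and 52 weeks. The secondary outcomes require non-union at 12 months, failure of fixation at all three visits and avascular necrosis at one year to be judged radiographically.

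**3. Radiologist.** A plate system and three separate screws differ in shape on a plain film. The article does not say so in words, but it follows from the two constructs described and needs no outside source. The article describes no masking of the images, and hiding the implant would defeat the assessment of fixation. The loss of blinding works on both sides of the comparison: a plate identifies Group 1, and the absence of a plate rules it out. So the reader of the films knows which side of the plate versus screws comparison (25 v 100) each participant is on.

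**4. Consultant deciding on re-operation.** The primary outcome is "The proportion of participants undergoing re-operation for failure of fixation within one year of sustaining the fracture". The Blinding section does not say that the consultant views the films. That step is an inference, though a strong one, since a decision to re-operate because fixation has failed can hardly be reached without imaging. The stated safeguard, that the consultant did not operate, withholds knowledge of what was injected. It does not withhold knowledge of what was implanted.

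**5. PRP versus control.** Groups 2 and 3 carry the same implant, so the radiograph gives no implant clue to separate them. The blinding statements can stand for this comparison (100 v 100).

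**6. Extent.** The unblinded arm is 25 of 225 participants (25/225 = 11.1%), and the affected comparison is 25 v 100. The article plans no formal check of whether blinding succeeded.

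**The case against.** The strongest reply is that the confirmatory trial is untouched. PRP versus control is the only comparison to be tested, its arms share the same screws, and the plate comparison is labelled hypothesis-generating with no formal inference. No p-value, error rate or sample size changes. All of that stands, and it limits the weight of the point. It does not make an unqualified statement about all outcomes true for the pilot arm.

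A second reply is that the consultant is independent of the trial and did not operate, which limits any motive for bias, and that the article never says the decision is made from films. Both parts are fair. The first reduces the risk of bias but does not create blinding. The second is why the loss of blinding for re-operation should be called very probable and not certain.

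A third reply concerns size. A reader might note that one altered decision among 25 participants moves the event rate by 1/25 = 4 points, and set this against the 15-point difference in the sample size section. The document does not support that reading. The 4 points are only 1/n and say nothing about how many decisions would change, and the 15 points were agreed for PRP, not for the plate. Sampling error is also far larger. At an assumed 30% event rate (the article cites 20-35% for fixation failure), the 95% half-width is 1.96 × √(0.3 × 0.7/25) ≈ 18 points for the pilot arm alone, and 1.96 × √(0.21/25 + 0.21/100) ≈ 20 points for the 25 v 100 difference. This objection stands: no magnitude of bias should be claimed.

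Finally, the treatment list already shows that the implants differ, so an attentive reader could work out the limitation. The blinding statements nevertheless say the opposite and should be corrected.

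**Conclusion.** The point holds for the plate versus screws comparison only. As written, the article claims assessor blinding for every outcome in every arm. For non-union, fixation failure and avascular necrosis, the radiologist cannot be blind to whether a plate is present. For re-operation, the consultant is very probably not blind either.

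The conclusion rests on two inferences: that the two constructs can be told apart on plain films, which follows from their description, and that the consultant uses imaging when deciding on re-operation, which the article does not state.

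A reader might infer that the trial's main result is compromised. The document does not support this, since the tested comparison uses one implant throughout. Participant blinding and the patient-reported EQ-5D are not challenged here. Any bias is confined to the descriptive rates and the effect estimate of the pilot comparison, and its size and direction are unknown. The correction is worth making because it costs almost nothing and changes what that estimate can be said to show.

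**What to change.** 1. In the Abstract (Design), the Design summary and the Blinding section, limit the assessor-blinding statements to the comparison of Group 2 with Group 3.
2. In the Blinding section and in the section on the fixed-angle comparison, state that radiographic outcomes are not assessor-blind when plate and screws are compared, and that the re-operation decision very probably is not.
3. When the pilot effect estimate is reported or used to plan a further study, describe it as open to assessor bias.

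The cost is wording only. Allocation, sample size, analysis and clinical care do not change. The downside is that the pilot arm's claim becomes slightly weaker.

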#### Trial treatments

All participants will have a closed reduction of their fracture. The lower limb will be supported on a fracture table. Internal fixation of the fracture will be achieved through a standard lateral approach with perioperative antibiotic cover in accordance with hospital protocol. Post-operative care will include early active mobilisation managed by a standard physiotherapy rehabilitation regime. All participants will have routine prophylaxis against deep vein thrombosis. Participants will be randomised to one of three groups:

1. Fixed-angle screw and plate fixation

2. Standard of care fixation and placebo injection

3. Standard of care fixation and PRP injection

#### Group 1: Fixed-angle screw and plate fixation

Fixation will be with the Targon FN Head Preserving System as described in the manufacturer's operative technique manual.

#### Group 2: Standard of care fixation

Fixation will be with three parallel cannulated screws. The exact configuration will be left to the discretion of the operating surgeon to ensure the results can be easily generalised. Fixation will be achieved using the standard operative technique.

#### Group 3: Standard of care fixation and PRP injection

Fixation will be with three parallel cannulated screws. The exact configuration will be left to the discretion of the operating surgeon to ensure the results can be easily generalised. Each screw will be advanced up to but not beyond the fracture such that no compression is achieved before the test substance is injected. The guidewire of one screw will then be removed and 5ml of PRP will be injected down the cannulated screw directly into the fracture site under image intensifier guidance. The guidewire will be immediately replaced and the screw/s will then be advanced to compress the fracture site.

#### Concomitant illnesses and medication

Concomitant illnesses and medication will be recorded at trial entry. Changes to these will be recorded at follow-up visits.

#### Interventions and assessments

Table 2 details the assessments and interventions that will be carried out during the period that each participant is involved in the trial.

**Table 2 T2:** Trial assessments and interventions

Serial	Intervention/Measurement	Time (weeks)
1	Operation	0
	Peri-operative complications	

2	AP & lateral radiographs	6
	MRI (subset of sample)	
	Clinical interview	

3	AP & lateral radiographs	12
	MRI (subset of sample)	
	Clinical interview	

4	AP & lateral radiographs	52
	MRI (subset of sample)	
	Clinical interview	

#### End of the trial

The trial will be closed when all participants have completed the one year follow-up visits. Once the trial is completed participants will be treated as per the standard of care.

#### Trial Flow diagram

See figure 1.

**Figure 1 F1:**
[figure not shown]
**Trial flow diagram**.

### Data management

#### Database and data management

Data to be collected from participants can be found at table 3. These data will be entered in the trial database. The trial database will be set up by the computer programmer and all specifications agreed between the computer programmer, statistician and trial co-ordinator. The procedure for data entry will be decided when the database is constructed. If electronic databases are required on computers external to the clinical trials unit, they will be compatible with the systems on site and backed-up accordingly. In the case of any interim analysis the database will be frozen at the analysis time point. Data collected after this point will not be included in the interim report.

**Table 3 T3:** Data to be collected during the trial

Serial	Intervention/Measurement	Time (weeks)
1	Peri-operative complications	0

2	EQ-5D score	6
	Radiographic union and fixation	
	Re-operation	
	Readmission	

3	EQ-5D score	12
	Radiographic union and fixation	
	Re-operation	
	Readmission	

4	EQ-5D score	52
	Radiographic union and fixation	
	Avascular necrosis	
	Re-operation	
	Readmission	

The case report forms will be designed by the Trial Co-ordinator in consultation with the Chief Investigator and statistician.

In the event of missing data the relevant clinical databases and case report forms will be accessed to complete the database.

#### Data access and quality assurance

All data collected will be anonymised after the collection of the baseline demographic data for each participant. Identifiable participant data will be held on a separate database and coded with a trial participant code to tag identifiable data to the outcome data.

All data will be stored in a designated storage facility in the Clinical Sciences Building on the research site at the University of Warwick. Data will be stored on password protected university computers in a restricted access building.

#### Archiving of trial data

Data will be archived in accordance with The University of Warwick clinical trials unit guidance.

#### Data monitoring committee

There will be a data monitoring committee convened for this trial.

### Statistical analysis plan

#### Analysis of efficacy

##### PRP vs standard-of-care (parallel cannulated screws)

The primary outcome measure, the proportion of patients requiring re-operation for failure of fixation within one year of sustaining the fracture, will be analysed using a chi-squared test for differences between internal fixation alone (control) and internal fixation and PRP (PRP) on an intention-to-treat basis. Treatments will be considered to differ significantly if p-values are <0.05 (5% level). Similarly, chi-squared tests will be used to assess the significance of observed differences for the secondary proportional outcome measures. If the numbers in the contingency tables are small (cells with values below 10) then Fisher's exact test will be used in preference to the chi-squared test. In addition to the main analysis, that will report treatment group effects for the primary outcome measure, a subsidiary analysis will use a multiple linear regression model to investigate the relationship between each patient's EQ-5D Score at 12 months and the treatment arm, age, gender, dementia and fracture displacement for each patient. Estimates, and 95% confidence intervals, from the regression model, and unadjusted results from t-tests will be reported and inferences made on the significance of the treatment effect. All analyses will be based upon an intention-to-treat analysis so missing data due to protocol violations will not be relevant. The primary outcome measure in this study has been chosen in order to limit the possibility of losing data from failed participant follow-up. The primary measure can be sourced from the patient, relative, GP or national hp fracture database.

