#### Power and sample size

The minimum clinically important treatment effect of PRP was agreed in discussion with several expert orthopaedic trauma surgeons. Although the figures varied by surgeon, all agreed that an absolute reduction of 15% in fixation failure would be clinically important. The overall rate of fixation failure of all intracapsular fractures of the femur is reported to be 20-35% [10]. Table 1 shows the total sample size with two-sided significance set at 0.05 for various scenarios of minimum clinically relevant difference. Sample sizes were determined using the PS power and sample size software [11].

**Table 1 T1:** Sample sizes calculated for various scenarios

Rate of failure in control group (%)	Rate of failure in the intervention group (%)					
	
	10		15		25	
	
	80% power	90% power	80% power	90% power	80% power	90% power
25	100	133				

30	62	82	121	161		

35	43	57	73	97	329	440

The mortality of patients with intracapsular fractures of the proximal femur is approximately 20% during the first year and this needs to be taken into account in the sample calculation. A recruitment target of 200 participants provides a good margin for unanticipated recruitment problems and loss to follow-up.

In the absence of an agreed method to determine the sample size for a pilot study a group of expert orthopaedic surgeons were consulted. All agreed that a sample of 25 participants in the fixed-angle screw and plate group would be sufficient to provide adequate pilot data.

From a recent audit carried out in our department we know that approximately 450 fractures of the proximal femur are treated operatively per year at University Hospital Coventry and Warwickshire. Approximately 250 of these patients would be eligible for inclusion into this trial. Therefore, even accounting for significant loss to follow-up, the trial sample can be recruited in one year.

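### The switch to Fisher's exact test at cell values below 10 does not say observed or expected; read as observed, it lets the failure counts choose the primary test and can replace the chi-squared test that Table 1 assumes

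*Protocol article*

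**What the plan says.** In the statistical analysis plan section on PRP vs standard-of-care, the primary outcome "will be analysed using a chi-squared test for differences between internal fixation alone (control) and internal fixation and PRP (PRP) on an intention-to-treat basis". The significance rule is: "Treatments will be considered to differ significantly if p-values are <0.05 (5% level". A sentence then extends chi-squared tests to the secondary proportions, and the switch follows: "If the numbers in the contingency tables are small (cells with values below 10", in which case Fisher's test replaces chi-squared. The condition refers to the contingency tables in general, so it can be read to cover the primary table as well as the secondary ones. It does not say whether the values are observed or expected, or whether one small cell is enough.

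The section on power and sample size sets "two-sided significance set at 0.05 for various scenarios of minimum clinically relevant difference" and adds: "Sample sizes were determined using the PS power and sample size software". On the effect to be detected, "all agreed that an absolute reduction of 15% in fixation failure would be clinically important". On the control rate: "The overall rate of fixation failure of all intracapsular fractures of the femur is reported to be 20-35" per cent. The sequence generation section plans 100 participants in each of the two main arms.

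**The concern.** Whether the chi-squared approximation is adequate depends on expected counts, conventionally with a threshold of 5. A threshold of 10 on observed cells measures something else. With 80 to 100 per arm and a 10% failure rate on PRP, the PRP failure cell is expected to hold 8 to 10 events, right at the threshold. Under one of the trial's own design scenarios, the observed failure count would therefore often decide which test is run. The replacement is the more conservative test, and the sample size made no allowance for it.

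At stake is some power where PRP failures are few, and the risk that a primary result significant by the planned test becomes non-significant for no reason of validity. The unclear wording adds to this: two analysts could read the rule differently and run different primary tests on the same data.

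**Working it through.** **Inputs.** Two-sided alpha 0.05, the control and intervention rates of Table 1, the 20-35% failure range, the 15-point reduction and first-year mortality of about 20% (power and sample size section); 100 per arm (sequence generation section). The protocol gives no evaluable number. 80 per arm is an assumption: 100 × (1 − 0.20) = 80.

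**Step 1: reproduce Table 1.** The uncorrected, pooled-variance formula is

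n per arm = [z(0.975)·√(2p̄(1−p̄)) + z(power)·√(p1(1−p1) + p2(1−p2))]² / (p1−p2)².

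For 25% vs 10% at 80% power, p̄ = 0.175:
[1.960·√0.28875 + 0.8416·√0.2775]² / 0.15² = (1.0532 + 0.4434)² / 0.0225 = 99.5, rounded up to 100.

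All 12 entries of Table 1 reproduce this way, as numbers per arm. (The text introduces them as totals; this does not affect the present point.) With a continuity correction, which behaves much like Fisher's test, 25% vs 10% would need 113 per arm. Table 1 therefore assumes the uncorrected chi-squared test.

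**Step 2: is chi-squared safe here?** At 25% vs 10% the expected failures per arm average 0.175 × 80 = 14 to 0.175 × 100 = 17.5. The probability that any expected count falls below 5 is about 0.000006 at 80 per arm. The exact size of chi-squared at 80 per arm, for null rates of 20, 25, 30 and 35%, is 5.0 to 5.2%. It needs no replacement.

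**Step 3: exact power under the rule.** Both binomials were enumerated in full. The rule was taken as Fisher if any observed cell is below 10, otherwise uncorrected chi-squared. Losses are from unrounded values.

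| Control vs PRP | Per arm | Rule triggers | Chi-squared | With rule | Loss (points) |
|---|---|---|---|---|---|
| 25 vs 10 | 100 | 45% | 81.6% | 80.7% | 0.9 |
| 25 vs 10 | 80 | 72% | 71.6% | 67.2% | 4.4 |
| 30 vs 10 | 80 | 72% | 90.3% | 88.8% | 1.5 |
| 30 vs 15 | 80 | 22% | 63.5% | 62.8% | 0.7 |
| 35 vs 10 | 80 | 72% | 97.7% | 97.4% | 0.2 |
| 35 vs 15 | 80 | 22% | 84.8% | 84.7% | 0.1 |
| 35 vs 25 | 80 | 0.2% | 28.5% | 28.5% | 0 |
| 20 vs 5 | 100 | 97% | 92.1% | 88.5% | 3.6 |
| 20 vs 5 | 80 | 99% | 84.9% | 79.4% | 5.6 |

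The 20 vs 5 rows are not in Table 1. They take the bottom of the quoted range less the agreed 15 points.

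**Step 4: type I error under the rule.** For null rates of 20-35% it is 4.5 to 5.1% at 80 per arm and 4.9 to 5.1% at 100.

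**Step 5: a concrete table.** With 8/80 failures on PRP and 18/80 on control:
chi-squared = 160·(18·72 − 8·62)² / (80·80·26·134) = 4.59, p = 0.032.
Fisher's test gives p = 0.052, although 13 failures are expected in each arm. With 9/100 vs 19/100 the p-values are 0.042 and 0.065.

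**Step 6: the expected-count reading.** If the threshold of 10 applies to expected counts, the rule triggers at 25% vs 10% in 3.1% of trials at 80 per arm (loss 0.2 points) and 0.09% at 100. It would still trigger at 20% vs 5%, in 46% of trials at 80 per arm and 11% at 100.

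**The case against.** The rule is stated in advance and errs on the conservative side, so it cannot produce extra false positives. Its sentence follows the one on secondary proportions, and its application to the primary table is not explicit. The primary outcome can be obtained from several sources, and death does not necessarily remove a patient from the analysis, so the analysed number may exceed 80 per arm. At the planned 100 per arm, the loss at 25% vs 10% is under one point. All of this stands, and it limits the size of the point. It does not justify a threshold that has no validity reason behind it, and the open reading, observed or expected, weakens the defence that the rule is purely mechanical.

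Three stronger readings are tempting and not supported:

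- A reader might infer that the rule triggers precisely when PRP works. It responds to low counts. With a true 15-point benefit at 80 per arm it triggers in 72% (25 vs 10), 22% (30 vs 15) or 3% (35 vs 20) of trials; with no effect at 10% vs 10% it triggers in 92%.
- A reader might infer a general loss of 4 to 5 points at 80 per arm. Within Table 1 that belongs to 25% vs 10% alone.
- A reader might infer a true type I error near 3%. Under the rule that requires a null failure rate of about 10%, below the protocol's stated range.

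**Conclusion.** The point holds in limited form. On the observed-cell reading, which is the natural one but not the only one, the rule lets the failure counts choose the primary test and can substitute a conservative test that the sample size did not assume. The cost is 0.9 points at 25% vs 10% with the planned 100 per arm, 4.4 points at an assumed 80, and 3.6 to 5.6 points at 20% vs 5%. Elsewhere in Table 1 it is small. Type I error is essentially unaffected for failure rates of 20-35%.

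The rule is not the main threat to power. At 25% vs 10%, going from 100 to 80 per arm costs 81.6 − 71.6 = 10.0 points under chi-squared; the switch then costs 71.6 − 67.2 = 4.4. The results assume independent binomial outcomes, equal arms and the switch applied to the primary table.

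**What to change.** Name one test for the primary outcome in advance, with no data-dependent switch: either the uncorrected chi-squared that Table 1 assumes, or its Cochran-Mantel-Haenszel version stratified by fracture displacement, which is the randomisation stratum. For the secondary proportions, state that an exact test is used only when an expected count is below 5.

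This costs one sentence in the analysis section and changes no data collection or trial procedure. The only downside is that the primary test rests on a large-sample approximation, which Step 2 shows to be accurate at these sizes.
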